### Analysis

#### Effectiveness

##### Individual Level

Descriptive statistics will be conducted to analyze feasibility outcomes, user engagement with the Jooay App, acceptability, and participation outcomes. Additionally, a hybrid inductive-deductive thematic analysis will be applied to analyze individual interviews to evaluate the app’s impact on user engagement and participation satisfaction.

##### Community Level

Engagement will be measured using a segmented linear regression model to analyze changes over time, including preintervention trends, immediate changes before and after the intervention, and postintervention trends. Where appropriate, models will account for autocorrelation, seasonality, and nonindependence of repeated observations over time. App usage data will capture time spent and interactions with gamification features, with descriptive statistics assessing usage patterns by province, disability, and age among youth participants. Outcomes available only in the gamified version, including planned and attended activities, satisfaction, and perceived achievement, will be analyzed descriptively and longitudinally during the postintervention period rather than included in the primary ITS comparison.

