### Objectives

The primary objective of this study is to evaluate whether the deployment of the gamified version of the Jooay App is associated with changes in app engagement compared with the previous nongamified version. Specifically, we will examine changes in app engagement following the deployment of the gamified Jooay App, using an interrupted time series (ITS) analysis of aggregated app analytics data.

The secondary effectiveness and feasibility objectives are to examine changes in specific engagement indicators, including app sessions, active users, duration of use, frequency of use, and use of key app features; to evaluate the feasibility of the gamified Jooay App among youth with disabilities, parents, and clinicians; and to explore postdeployment participation-related outcomes, including planned activities, attended activities, satisfaction, and perceived achievement.

The implementation objectives are to assess the process of implementing and scaling up the gamified Jooay App across participating Canadian provinces; to describe the expansion, role, and activities of the Jooay KB networks across these provinces; to identify provincial barriers and facilitators influencing app uptake, implementation, and sustainability; and to examine how the app and KB networks support the identification of community-based play and leisure opportunities for children and youth with disabilities.

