### Theoretical Framework

In this study, we will use the CFIR to implement and evaluate the scale-up and expansion of the app use through the expansion of KB networks [22]. KB networks will mobilize information about the app and foster engagement with the app and community activities. We will use the health behavior framework to guide the individual intervention evaluation for the user-designed gamification features to increase individual engagement with the app [23].

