#### Implementation

The KB strategy will be implemented and evaluated using an ITS. This approach is well-suited for assessing the effectiveness of population-level health interventions and testing their impact on specific outcomes within a defined impact model. We will conduct a multisite ITS study, accounting for the KB interventions in 5 different provinces. KBs who participated in previous Jooay studies will be invited to participate in a focus group to (1) review past KB practices, (2) rank strategies based on perceived effectiveness, (3) identify contextual factors influencing implementation, and (4) refine strategies for different settings. New KBs will be recruited and trained through interactive online workshops in purposefully selected provinces (British Columbia, Alberta, Saskatchewan, Ontario, Québec, and Yukon) and across sectors (families, youth, health, and education). KBs will identify new activities, update program information in their provinces, identify populations who may not know about the app, and develop strategies to disseminate within these provinces and promote the app to users (youth, families, clinicians, and educators) and community organizations within their scope of reach. Their insights will inform a 2-fold approach to innovation, sustainability, and use: (1) an automated system to optimize resource identification and updates within the Jooay database, and (2) an organic, human, and community-led dissemination process.

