### Sample Size

This study includes three different sample-size considerations: (1) the ITS analysis of app engagement outcomes at the population level; (2) the recruitment of KBs to support the implementation of the app across Canadian provinces; and (3) qualitative interviews with KBs and feasibility study participants. Because these research components have different research objectives, the sample-size rationale differs across study components, as described below. For the ITS analysis, the primary unit of analysis will be the repeated time interval. ITS emphasizes the importance of repeated observations, underlying trends, and seasonal patterns when evaluating population-level interventions introduced at a clearly defined time point [24]. Therefore, engagement outcomes will be extracted from in-app analytics and aggregated monthly at the community level across all eligible app users. We will include a minimum of 12 monthly time points before and 12 monthly time points after the deployment of the gamified version of the Jooay App.

KBs will serve as provincial implementation partners who support raising awareness about the app across Canada. We will recruit at least 1 KB from each target province, for a minimum of 6 KBs, with the possibility of recruiting up to 2 per province where feasible. This will be determined during the preimplementation phase with current KBs and patient and community partners of the Jooay App research team. This approach will help us ensure sufficient representation across Canadian provinces, Jooay user types (eg, clinicians and parents), and communities with varying availability of adaptive and inclusive leisure activities. Qualitative interviews do not preclude a sample size. Purposeful, maximum variation sampling will be adopted to recruit KBs and feasibility study participants across sectors and regions of interest, with varied experiences and levels of engagement with leisure and their communities. We will also aim to recruit participants in regions where we know there is a limited offer of community-based activities to develop strategies that can support increased participation at the individual and community levels.

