Following the completion of the pilot feasibility study, the gamified version of the app will be deployed to all users at the community level. The date of deployment of the gamified version will serve as the intervention point for an ITS analysis. This design was selected because gamification will be introduced at the app or community level and cannot be randomized across users once it is deployed. The ITS design will allow us to examine whether the introduction of the gamified version is associated with changes in the level and/or trend of engagement outcomes compared with patterns observed during use of the previous nongamified version. Engagement data will be extracted from in-app analytics and aggregated at monthly intervals. The preintervention segment will include monthly data from the previous nongamified version of Jooay, and the postintervention segment will include monthly data after deployment of the gamified version. We will include a minimum of 12 monthly time points before and 12 monthly time points after deployment to allow the estimation of baseline trends, postintervention changes, and seasonal patterns. Seasonality will be assessed through visual inspection of monthly trends. If seasonal patterns are identified, models will include calendar month indicators. We will also document other major app updates, holidays, school calendar periods, or external events that may influence engagement and consider these in adjusted or sensitivity analyses. Engagement outcomes will be measured using both backend and frontend indicators. Backend engagement measures will include app usage frequency, number of accesses, duration of use, and feature usage as captured through in-app analytics. Frontend engagement measures will include engagement with community-based features for youth users and the inclusion of community play and leisure activities within intervention plans developed by clinicians and educators. Additionally, following the deployment of the gamified version, participation in leisure will be assessed using newly co-designed in-app features that capture the number of activities users plan and attend, as well as users’ self-reported satisfaction and perceived achievement. These outcomes will be examined descriptively and longitudinally during the postintervention period to explore patterns of participation over time and their association with app engagement.

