### Community Level

The effectiveness of the gamification-based mobile app intervention will be assessed primarily through user engagement metrics collected through app analytics, including the number of clicks, logins, active time spent, access frequency of individual gamification features, comments, and reviews. These data will provide insights into how youth, caregivers, and professionals interact with the app over time. Additionally, differential outcomes will be examined for health care and education professionals, focusing on the integration of community participation into intervention plans and health promotion strategies. For youth, the impact of the intervention will be evaluated based on increased participation in community activities, collected from the “Activity Planner” and “My Summary” features within the Jooay App.

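### The primary time series pools all users while the study's own outreach seeks to bring in new ones, so a shift at release cannot alone be read as individual engagement

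*Protocol article*

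**What the plan says.** The primary objective in the protocol article (Objectives) compares the gamified with the nongamified app "using an interrupted time series (ITS) analysis of aggregated app analytics data". Under Sample Size, engagement is "aggregated monthly at the community level across all eligible app users", and the plan continues: "We will include a minimum of 12 monthly time points before and 12 monthly time points after the deployment". Under Procedures, Effectiveness: "The date of deployment of the gamified version will serve as the intervention point for an ITS analysis".

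Under Analysis, Effectiveness, Community Level, the model is a segmented linear regression. It allows, where appropriate, for serial correlation, season and repeated measurement. Procedures, Effectiveness adds other app updates, holidays, the school year and outside events as matters for adjusted or sensitivity analyses. Neither list names user type, account age or broker outreach. The usage breakdowns are "descriptive statistics assessing usage patterns by province, disability, and age among youth participants".

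The users are mixed: Variables and Outcomes, Community Level wants to learn "how youth, caregivers, and professionals interact with the app over time". Theoretical Framework gives the two components different jobs. Broker networks spread the app, and the evaluation at individual level concerns "user-designed gamification features to increase individual engagement with the app".

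Under Sampling, Implementation, brokers are to "identify populations who may not know about the app, and develop strategies to disseminate". Procedures, Implementation has them promote the app to families, young people, professionals and organisations over six months, with a workshop on the gamified version at the second meeting. Variables and Outcomes, Implementation counts growth in users as an outcome.

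**The concern.** A monthly aggregate over whoever is active combines how much each kind of user uses the app with how many of each kind there are. Gamification is meant to change the first. Outreach is meant to change the number of users and may change their mix. If both happen near the breakpoint, the segmented model cannot separate them.

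Dividing by the number of active users does not solve this, because it fixes the count and not the mix. An influx of accounts in an active first few weeks would look like a gain from gamification. A rising share of professionals who open the app less often would look like a loss, or would hide a real gain. What is at stake is how the main result is interpreted: engagement in the user population may have changed without anyone responding to the new features.

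**Working it through.** The plan gives no power, effect size or variance for the time series, and the 12 + 12 months are a minimum count. There is no stated figure to reproduce. The steps below check whether the mechanism works and how large it could be. **All mixes, rates and noise levels are assumptions, not figures from the protocol.**

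**1. Timing.** Results gives data collection from March 2026 to June 2027, which is 16 months. If the 12 post-release months fall inside that window, the first is at the latest month 16 − 12 + 1 = 5, July 2026. A six-month broker period starting in March 2026 runs to August 2026 and straddles release. The start of outreach is not stated, so overlap is probable, not certain.

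**2. Change in mix alone.** Per-user mean = p × (rate in new accounts) + (1 − p) × (rate in older accounts), where p is the share of new accounts.
- Rates 4 and 1.5 sessions a month, p = 15%: 0.15 × 4 + 0.85 × 1.5 = 1.875. With p = 25%, 30%, 35%: 2.125, 2.25, 2.375, that is +13%, +20%, +27%.
- Rates 3 and 2: 2.15 before; 2.25 to 2.35 after, that is +5% to +9%.
- User type: families 3, professionals 1.5, professional share 40% to 55%: 0.6 × 3 + 0.4 × 1.5 = 2.40 becomes 0.45 × 3 + 0.55 × 1.5 = 2.175, that is −9%.

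**3. What the planned model reports.** Least squares on 24 noise-free months with intercept, time, level change at month 13 and slope change; p moves from 15% to 25–35%. In the ramp, p rises in six equal monthly steps from the first post-release month.

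| Course of the mix | Rates | Level change | Slope change per month |
|---|---|---|---|
| Immediate and lasting | 4 v 1.5 | +13% to +27% | 0 |
| Immediate, ends after 6 months | 4 v 1.5 | +16% to +32% | −1.7% to −3.4% |
| Ramp over 6 months | 4 v 1.5 | +5% to +10% | +1.0% to +1.9% |
| Ramp over 6 months | 3 v 2 | +2% to +4% | +0.3% to +0.7% |

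**4. A second set of assumptions.** Users 20% youth, 50% parents, 30% professionals, with 6, 4 and 2 sessions: mean 0.2 × 6 + 0.5 × 4 + 0.3 × 2 = 3.8. Outreach adds 25% new accounts at release.
- Newcomers 10/20/70 (mostly professionals, mean 2.8): (3.8 + 0.25 × 2.8)/1.25 = 3.60, −5.3%.
- Newcomers 70/20/10 (mostly youth, mean 5.2): (3.8 + 0.25 × 5.2)/1.25 = 4.08, +7.4%.
- Spread over six months from release: level −2.3% or +3.2%, slope −0.36% or +0.50% per month.
- Same type mix, newcomers half as active: (1 + 0.25 × 0.5)/1.25 = 0.90, −10%.
- Totals instead of per-user means, newcomers at release: 0.25 × 2.8/3.8 = +18.4%, or 0.25 × 5.2/3.8 = +34.2%.
- Newcomers with the same mix and activity: per-user change 0.
- Series standardised to fixed user-type weights, where only type matters: level and slope change 0.

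**5. Would it be declared significant?** The standard error of the level change is 0.821 × residual SD, with 24 − 4 = 20 degrees of freedom, two-sided 5%, independent errors. At SD 10% of baseline:
- artefact of 15%: 0.15/0.0821 = 1.83, significant in 41% of series;
- artefact of 25%: 0.25/0.0821 = 3.05, 83%;
- artefacts of 5% and 9%: 9% and 18%;
- ramps in step 3: 9–23% with 4 v 1.5, about 5–7% with 3 v 2.

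Simulation of the shifted type mixes in step 4 with 25% new accounts (4,000 series each) gave 9–13% if all join at release and 6–7% over six months (starting at release or two months before) at SD 10%. At SD 3% it gave 53–81% and 13–37%. With no change in mix it gave 4–6%.

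**The case against.** The strongest objection is that the stated question concerns the population. Objectives asks about change in aggregated engagement and lists active users among the indicators. If gamification attracts or retains users, who is active is part of the effect, and a series standardised to the earlier mix would remove it. This stands. A reader might infer that the pooled series is wrong and must give way to a standardised one; the documents do not support that. Nor is dilution an error: a 30% gain confined to families and youth reads as 30% × (1 − 0.3) = 21% or 30% × (1 − 0.6) = 12% if professionals make up 30% or 60% of activity, and that is a correct population average.

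The protocol also never fixes a per-active-user metric. That is so, but step 4 shows that totals move more.

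The breakdown wording can be read with the youth restriction attached only to age, or to disability and age, so it should not be taken as excluding every breakdown for adults. On either reading it is descriptive and does not name user type or account age. The separate outcomes planned for professionals concern intervention plans, not the engagement series.

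KB Intervention Evaluation plans a multisite time series accounting for broker activity, but nothing says that the release analysis is adjusted for it. A separate analysis plan may define eligible users more narrowly or add strata. What the article does state is pooling over all eligible users and a list of adjustments that omits the study's own outreach. Finally, Setting, Implementation says brokers were used before in these regions, so the baseline may already reflect some outreach.

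**Conclusion.** The concern holds as a limit on interpretation. The pooled series can answer whether aggregate engagement changed. It cannot by itself show that users engage more because of gamification, since a change in user mix near release can give a level or slope change in either direction.

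The size cannot be determined from the documents. It is zero if newcomers resemble existing users, and about 2% to 30% in the fitted level change across the account-age scenarios in step 3. The upper end needs strongly different usage rates and an immediate shift. With a six-month build-up the level change is 2–10% and the rest goes into the slope.

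A reader might infer that a false positive is likely. The 41–83% rates apply only to artefacts of 15–25%. Gradual outreach at the same 10% noise gives about 5–23%, and the milder type shifts 6–13%. The calculations assume independent errors, and the overlap of outreach with release is inferred.

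**What to change.** Under Analysis, Effectiveness, Community Level, keep the pooled aggregated series as the primary population-level analysis and prespecify alongside it:

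- (a) the same segmented model by user type (youth, parent, professional);
- (b) a sensitivity analysis standardised to the pre-deployment user-type mix, or split by account age, where the analytics export allows;
- (c) the numbers of active and new users in each stratum, as series of their own.

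State that a change will be attributed to individual engagement with gamification only if it persists in (a) and (b).

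One caution on (b): accounts opened before release are an obvious subset, but it contains no new accounts afterwards. If new accounts are the more active ones, it drifts down unaided (at 4 v 1.5, from 1.875 to 1.5, −20%, once none is new). An account-age split defined identically in every month avoids this.

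The cost is analysis wording and a stratified export, with no extra participants. Small strata will be noisier and may need merging. The export must carry user type and registration date, also for the nongamified months. The documents do not confirm this, and Ethical Considerations says analytics are analysed in aggregate, deidentified form, so availability should be checked first. Results reports that the time series study had not begun at submission, so this can still be prespecified.

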### Implementation Process Evaluation

To assess inner and outer settings, we will use the Child Health Initiatives Limiting Disability-Community Health Inclusion Index (CHILD-CHII) [29]. This tool will identify key characteristics to tailor dissemination strategies, expand KB networks, and enhance user engagement. KBs will also participate in a training workshop and complete the Policymakers’ Information Use Questionnaire (POLIQ; an intention-to-use information tool from the CHILD-BRIGHT (Child Health Initiatives Limiting Disability–Brain Research Improving Growth and Health Trajectories) Knowledge Translation [KT] program, phase I) to assess individual characteristics, including KBs’ beliefs, knowledge, self-efficacy, and personal attributes [30].

### KB Intervention Evaluation

We will conduct a multisite ITS study, accounting for the KB interventions in 5 different provinces. We will then summarize data across several sites (provinces) to evaluate the overall impact of the implementation interventions [31]. Post hoc evaluation will include subgroup analyses for the different types of KBs (health care providers, families, youth, and community organization representatives) and the number of activities listed in each province by population density.

### Patient and Public Involvement Statement

Patients, including youth with disabilities and their families, were involved in the research from the early stages of the project—and will continue to be in this phase of the project. The PWLEs, including youth with disabilities and their families, played a key role in shaping the research questions, ensuring that the study’s focus aligns with their priorities, experiences, and preferences. The development of the research questions was informed by the lived experiences of patients and public stakeholders, particularly regarding the accessibility and impact of leisure activities in the community, a key policy priority for this study. PWLEs codeveloped the user-centered design of the Jooay App, focusing on gamification features, and will help create accessible informational materials for KBs and users. Their feedback also influenced the choice of outcome measures, emphasizing community participation and awareness of leisure activities. PWLEs help inform the choice of dissemination strategies, ensuring that results will be shared meaningfully through social media and networks like Jooay and CHILD-BRIGHT, keeping participants and communities informed throughout the study.

### Ethical Considerations

This study was approved by the McGill University Institutional Ethics Review Board (22-05-070). Participants will provide informed consent, and confidentiality will be maintained throughout the study. For children, parental or caregiver consent will be obtained, and child assent will be sought, using language appropriate to the child’s development. Participants will be informed that their participation is voluntary and that they may withdraw from the study at any time without any negative consequences to their access to services or their use of the Jooay App. As the study involves children and youth with disabilities, app analytics, user behavior data, and participation-related data, additional safeguards will be put in place to ensure privacy and confidentiality. App analytics will be analyzed in aggregate and deidentified form, and personally identifiable information will be removed prior to analysis. Qualitative interview data will be deidentified in transcription and analysis.

All electronic data will be stored on secure, password-protected institutional servers (OneDrive folders) and will be accessible only to authorized members of the research team. Findings will be reported in aggregate form to protect individual users, families, KBs, and regions. Participants will be provided with accommodations during study procedures (eg, interviews) and other research activities. The research team will monitor for participant discomfort or burden, and participants may skip any question or stop participation at any time.

